# Abbreviations

ET Exercise training

ACE Angiotensin converting enzyme

ARB Angiotensin receptor blocker

BMI Body mass index

BP Blood pressure

CAD Coronary artery disease

CAG Coronary arteriography

CI Confidence interval

CPET Coronary-pulmonary exercise test

CFVR Coronary flow velocity reserve

CMD Coronary microvessel dysfunction

DEXA Dual X-ray absorptiometry array

FEV1 Forced expiratory volume first second

FMD Flow mediated (vaso)dilation

HADS Hospital Anxiety and Depression Scale

LAD Left anterior artery

LED Low energy diet

LVEF Left ventricular ejection fraction

NBV Nationale behandlingsvejledning (Dansk Cardiologisk Selskab)

NO Nitric oxide

NTG Nitroglycerine

RER Respiratory exchange ratio

SAQ Seattle angina questionnaire

SD Standard deviation

STEMI ST-elevation myocardial infarction

NSTEMI non-ST-elevation myocardial infarction

TTDSE Transthoracic Doppler stress echocardiography

# Background

Angina pectoris is the most common symptom of coronary heart disease among women but unlike men most women do not have stenosis of the coronary arteries.^1^ ^2^ ^3^ ^4^ Recent studies emphasize that contrary to previous understanding many of these women have a poor

prognosis.^5^ We have recently confirmed this in a Danish population where two thirds of

women referred to invasive angiography had no obstructive coronary disease. This

proportion has increased in the last decade and is associated with frequent hospital readmission, continued angina, loss of quality of life and a five times higher risk of

premature exit from the work force than the background population.^4^ ^6^ ^7^ Thus, there are considerable financial and human costs associated with non-obstructive angina in

women.^8^ Mean age at debut is 57 years^4^ and with an estimated 40.000 women in Denmark

suffering from the condition the benefits from improved care are substantial. Through

clinical and pathological studies microvessel disease as a cause of ischemia, angina and

poorer prognosis has emerged.^9^ ^10^ ^11^

*Microvessel disease*

In the heart 95% of the blood flow is controlled by the microcirculation, **Figure 1.**When oxygen demand is increased the normal response of the microvessels is to reduce resistance in order to increase flow. When microvessels are dysfunctional the blood flow in the larger coronary vessels does not increase sufficiently to meet oxygen demand, thus leading to ischemia and pain. The main causes are thought to be dysfunction of endothelium and structural changes such as perivascular fibrosis and changes in vascular smooth muscle cells. In addition to vasodilation the endothelium plays a central role in the atherosclerotic process by generating vasoactive and anticoagulant factors that are important mediators of thrombosis. Coronary microvessel dysfunction (CMD) has been shown to be a strong predictor of poor cardiovascular prognosis in a wide group of cardiac patients.^12^ ^13^ ^14^ ^15^ ^16^ ^17^

*Proof of concept*

Although microvessel disease is thought to be the cause of angina in a large proportion of patients, CMD is also demonstrable in asymptomatic individuals with cardiovascular risk factors. Data derived from eastern Denmark indicate that more than 50% of women with angina have CMD^4^ but comparative studies of the prevalence of CMD in asymptomatic individuals have not been performed. Thus, CMD may merely be an innocent bystander related to the presence of cardiovascular risk factors rather than the cause of angina symptoms. Furthermore, only a handful of interventional studies have simultaneously addressed CMD and symptoms in this patient group and with diverging results.^18^ ^19^ Thus there is a need of studies showing ‘proof-of-concept’, i.e. that improvement of CMD also improves angina symptoms in these patients.

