### Hypothesis

CMD is the cause of angina pectoris in a large proportion of women with angina. Intervention that improves CMD also leads to amelioration of symptoms and improved prognosis.

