# Aims

The aim of this study is a ‘proof-of-concept’, i.e. to determine whether a comprehensive

intervention is feasible and results in improvement in both angina and CMD.

The study is a pilot study which we, if successful, will seek to expand to a multicenter interventional trial with prognostic outcome in collaboration with an international

consortium.

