# Methods

Sixty participants are included, examined at baseline and randomized (1:1) to either comprehensive treatment or usual care (controls). Comprehensive treatment consists of 24 weeks of LED, exercise training and optimized medical treatment. Usual care is medical treatment handled by the researcher, MD, at baseline and follow-up. In case of delay, e.g. cancellation of appointments by the participants, four weeks are accepted between baseline assessments and start of intervention (week 0, defined by the first (baseline-) meeting with dietician). A delay of up to four weeks (eg. cancellation) is accepted.

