## Intervention

The components and goals of the intervention are outlined in **Table 2.** The main

components are:

- Body weight loss without significant loss of muscle mass, through low energy diet combined with
- Exercise training based on interval training and resistance exercise^20^
- Optimal medical treatment for hypertension and hypercholesterolemia (with statin and ACE-inhibition)
- Risk factor control: smoking cessation aid, nutrition counselling, screening and treatment for diabetes

DEXA scan and exercise capacity measurements are primarily used to ensure and monitor efficiency of exercise and weight loss interventions. The intervention program involves a multidisciplinary approach provided by a team of dieticians, physiotherapists and doctors trained in cardiac rehabilitation. Attention will be given to program flexibility combining structured group-based protocols with individually tailored strategies.

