# Statistics

## Sample size

The primary endpoint is change in microvascular function assessed by CFVR.

We wish to be able to detect a difference in change in CFVR between groups of 10%, equal to a change in CFVR of 0.24, assuming a baseline mean CFVR of 2.4. According to our previous study (22) the standard deviation of the within individual change is assumed to be 0.3. With power of 0.8 and two-sided significance level of 0.05, 26 patients should be included in each group. With 26 in each patient group we will be able to detect a moderate or larger effect on symptom burden. Anticipating dropout, randomization of a total of 60 patients was chosen. Dropout within the first three weeks of inclusion is replaced by new inclusion.

SAQ has four subscales each with a score from 1-100. We have not found data on within-study subject variation on SAQ. However, previous trials have obtained changes in SAQ of 10-20 points after intervention.^18^ ^46^ ^13^ A trial of 46 patients (predominantly women) with microvascular angina randomized to either ranolazine, ivabradine or placebo for four weeks found a SAQ score change of 10-40 points across different SAQ parameters, all highly significant (p<0.001).^18^ We will conduct a study on a similar study population, and we therefore expect to have the statistical power to document clinically relevant effects.

With 60 participants included, the probability is 80 percent that the study will detect a treatment difference at a two-sided 0.05 significance level, if the true difference between treatments is 11. This is based on the assumption that the standard deviation of the response variable is 15.

Analyses will be performed in STATA/IC 13.1. Categorical data will be presented as number (percentage), continuous data as mean (SD) or median (interquartile range) if normal distribution cannot be assumed. Regression analysis will be performed with the primary outcome change in symptoms (SAQ) and the independent variable change in CFVR.

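### The stated regression of SAQ change on CFVR change cannot tell CMD as the cause of angina from a package that improves both by separate routes

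*Protocol*

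**What the plan says.** - **Background, Proof of concept.** The protocol notes that CMD also occurs in people with risk factors but no symptoms, and concludes that "CMD may merely be an innocent bystander related to the presence of cardiovascular risk factors rather than the cause of angina symptoms". It asks for studies showing "that improvement of CMD also improves angina symptoms in these patients".
- **Hypothesis.** "CMD is the cause of angina pectoris in a large proportion of women with angina".
- **Aims.** More modest: whether the "intervention is feasible and results in improvement in both angina and CMD", in a pilot that may lead to a multicentre trial.
- **Methods and Intervention.** One arm receives everything: "Comprehensive treatment consists of 24 weeks of LED, exercise training and optimized medical treatment". The component list adds "Risk factor control: smoking cessation aid, nutrition counselling, screening and treatment for diabetes". The comparator is usual care, and no arm isolates CMD.
- **Blinding.** Participants know their allocation, and SAQ is self-reported.
- **Statistics, Sample size.** "Regression analysis will be performed with the primary outcome change in symptoms (SAQ) and the independent variable change in CFVR". No term for arm, weight, blood pressure, fitness or medication is named.

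**The concern.** The hypothesis is a statement about a pathway: a better microcirculation leads to less angina. The package has other possible ways to reach SAQ, namely risk-factor change, fitness, medication and open-label reporting. If any of them operates, CFVR change and SAQ change will be associated even when neither causes the other.

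This can happen in two ways. Pooling the arms turns two separate treatment effects into one slope. Within the intervention arm, women who respond more to the package may improve more on both measures. An arm term removes only the first.

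At stake is the reading of a positive result. A joint gain with a significant slope could be taken as support for CMD as the cause of angina, although the stated model cannot separate that from parallel effects of the package.

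**Working it through.** **1. The plan's own figures.** CFVR difference 0.24, SD of change 0.3, power 0.8, two-sided 0.05: the t-test solution is 25.5, so 26 per group, as stated. SAQ difference 11, SD 15, 30 per group: power 0.798 by t-test, against the stated 80%. Both reproduce. The issue is what the regression identifies, not the sample size.

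**2. Arm difference alone.** Use the protocol's effects, reading the SD of 15 as the SD of SAQ change. Assume no CFVR-SAQ link and no correlation within arms. With equal arms, pooling adds (difference)²/4 to each variance and the product of the differences/4 to the covariance:

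- covariance = 0.24 × 11 / 4 = 0.66
- variance of CFVR change = 0.3² + 0.24²/4 = 0.1044
- variance of SAQ change = 15² + 11²/4 = 255.25
- pooled correlation = 0.66 / √(0.1044 × 255.25) = 0.128

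Fisher z approximation: atanh(0.128) × √(n − 3) is 0.90 at n = 52 and 0.97 at n = 60. The chance of exceeding 1.96 is then about 14% and 16%. Simulation (20,000 trials per setting) gives 14.3% and 16.3% significantly positive slopes, against a nominal 2.5%. Adding arm brings this back to 2.4-2.5%.

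**3. Shared response within arms.** Assume one composite risk-factor change that differs by 1 SD between arms. Each outcome change has within-arm correlation r with it, and CFVR has no effect on SAQ. The two changes then correlate r² within arms. The protocol gives no value for r, so it is ranged. Two-sided rejection rates of the CFVR slope (nominal 5%):

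| r | r² | Arm in model, n = 52 | Arm in model, n = 60 | Arm and risk-factor change in model |
|---|---|---|---|---|
| 0.2 | 0.04 | 6% | 6% | 5% |
| 0.3 | 0.09 | 10% | 10% | 5% |
| 0.4 | 0.16 | 21% | 22-23% | 5% |
| 0.5 | 0.25 | 43% | 48-49% | 5% |

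Hand check at r = 0.5, n = 60: atanh(0.25) × √(60 − 4) = 1.91, and the chance of exceeding 1.96 is about 48%.

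In the model as written, r = 0.4-0.5 gives about 28-64%. If the composite is measured with reliability 0.8, the adjusted rate is 5-8%.

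**4. Availability of covariates.** Table 1 schedules blood pressure, BMI and anthropometry, and the VO2 test, at baseline and week 24. Body weight is a secondary endpoint and is listed under Clinical examination.

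**The case against.** **The rival does not by itself predict a joint gain.** A reader might infer that the protocol's bystander account predicts exactly the same data as the causal one, so that the trial cannot test its hypothesis at all. The text does not support this. The bystander account is drawn from people with risk factors and CMD but no angina. It ties CMD to risk factors and does not say that risk factors cause angina. On that reading, treating risk factors would raise CFVR and leave SAQ unchanged, which the trial can show and which would count against the hypothesis. A joint gain needs an added route from the package to angina outside CMD. The package contents, the benefits expected under Risks and the unblinded SAQ make such a route plausible but do not establish it. This part of the objection stands.

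**The aim is modest.** The randomised comparisons answer whether the package improves each outcome, and no passage says that a significant slope will be declared proof. That stands too. It limits the point to the mechanistic claim in the Hypothesis.

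**The model may be fuller in the SAP.** An SAP, not shown here, may add covariates. That would help, but an arm term alone does not cure the within-arm part, as step 3 shows.

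**Correlations of 0.4-0.5 are at the high end.** The procedure section gives a repeatability coefficient of 0.70, so an SD of repeat differences of 0.70/1.96 = 0.36. It also gives a coefficient of variation of 11%, so 0.11 × 2.4 × √2 = 0.37. Both exceed the assumed SD of change of 0.3. Even the 7% found in healthy subjects gives 0.24, which is about 63% of the variance (0.24²/0.3², from the unrounded 0.2376), and caps any correlation with CFVR change near √0.37 = 0.61. These figures come from other populations, but the lower rows of the table deserve less weight.

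**Adjustment can hide a true link.** VO2peak may rise because angina eases, so adjusting for it can bias the CFVR slope. If CFVR truly drives SAQ with a within-arm correlation of 0.3-0.4, a model with arm detects it in about 58-89% of trials. Illustrative causal runs give about 51-85% with weight and systolic pressure added, and 32-75% if VO2peak is added and responds to angina. This rules out a rule that accepts the link only if the adjusted slope stays significant.

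**Conclusion.** The concern holds in a limited form. The stated regression, pooled over arms with no other term, cannot distinguish CMD as the cause of angina from a package that improves CFVR and angina by separate routes.

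The firmest figure is 14-16% false positive links from the arm difference alone. It uses only the protocol's effect sizes and assumes that the whole SAQ gain comes by another route. The excess that survives an arm term depends on assumed correlations: slight at 0.2, about double the nominal rate at 0.3, and large only at 0.4-0.5.

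The trial is not uninformative about the hypothesis: a CFVR gain without an SAQ gain would speak against it. The randomised comparisons serving the aim are untouched. The change is worth making because it is cheap and bears on how a positive pilot is interpreted.

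**What to change.** In the Statistics section:

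1. Keep the simple model and report beside it one pre-specified model of SAQ change on CFVR change, arm, change in body weight and change in systolic blood pressure.
2. Show a version that also adds change in VO2peak only as a sensitivity analysis, and say that VO2peak may be partly a result of less angina.
3. Report the CFVR slope with its confidence interval from each model, with no pass/fail significance rule.
4. State that joint improvement shows that the package improves both outcomes, and that the slope is an association consistent with, but not proof of, CMD as the cause. Align the Hypothesis wording with this.

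The cost is wording and extra regressions on data already scheduled. The interval for the slope will be wider and power for a true link modestly lower. Confounding will remain, because weight and systolic pressure capture only part of the risk-factor response and neither captures medication or open-label reporting.

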**Figure 1:**

Photo illustrating extent of coronary microvasculature in relation

to epicardial vessels. Brought with permission from [name].

### Rationale for intervention

In women with angina and no obstructive stenosis of the coronary vessels cardiovascular risk factors are common. Among 3000 Danish women with angina and open arteries, 12% had diabetes, 48% hypertension, 20% were smokers and the mean body mass index (BMI) was 27 kg/m^2^.^4^ In a randomized trial among overweight patients with coronary artery disease (CAD) we have recently found that both a large weight loss and intensive exercise training significantly improve coronary flow velocity reserve (CFVR).^20^ ^21^ Small studies addressing risk factors individually suggest an effect on peripheral vascular function of exercise training,^22^ ^23^ statin therapy, and weight loss.^24^ ^25^ Eighty percent of women with CMD have pre-diabetes, which is strongly associated with microvessel disease. Lifestyle intervention significantly reduces risk of developing diabetes.^26^ Medical treatment targeting microvessel dysfunction in patients with angina has not been systematically tested but small studies indicate an effect of beta-blockers ^27^ and Angiotensin Converting Enzyme (ACE)-inhibition^18^ on coronary microvessel function.^24^ Thus, small studies indicate effect of individual interventions but mainly on the function of peripheral vessels. A comprehensive intervention simultaneously targeting CMD and angina has not previously been attempted. The rationale for this present intervention is to test this concept in women with angina and CMD.

### Hypothesis

CMD is the cause of angina pectoris in a large proportion of women with angina. Intervention that improves CMD also leads to amelioration of symptoms and improved prognosis.

# Aims

The aim of this study is a ‘proof-of-concept’, i.e. to determine whether a comprehensive

intervention is feasible and results in improvement in both angina and CMD.

The study is a pilot study which we, if successful, will seek to expand to a multicenter interventional trial with prognostic outcome in collaboration with an international

consortium.

# Study design

The study is a randomized, controlled intervention trial. Patients from the iPower cohort fulfilling the inclusion criteria of this present study are invited to participate. Please see **figure 2** for a schematic overview of the inclusion. Details regarding the study information and informed consent are further described in the chapter “Ethical aspects”. Sixty participants are included in the study. After baseline examinations participants are randomized (1:1) to either comprehensive intervention for 24 weeks or usual care (controls). Baseline and 24-week assessments are performed at the Hospitals Bispebjerg and Frederiksberg. Please see **Table 1.**

## Randomization

A third party unrelated to the study will perform randomization of participants with randomly permuted block sizes of 2,4, and 6 using the ralloc program in Stata 11. Replacement of participants will be possible in case of dropout.

## Figure 2. Flowchart of the study

## Table 1. Schematic overview of data assessments

| **Table 1** | Time (min) | **Baseline**  **Week 0** | | | **Follow-up**  **Week 24** | | |
| --- | --- | --- | --- | --- | --- | --- | --- |
|  |  | stud med | MD | physio | stud med | MD | physio |
| Informed consent | 10 | x |  |  |  |  |  |
| In- and exclusion criteria |  |  |  |  |  |  |  |
| General health examination |  |  |  |  |  |  |  |
| Medical history | 10 | x |  |  | x |  |  |
| ECG | 10 | x |  |  | x |  |  |
| Blood pressure, heart rate, BMI, anthropometry, ECG | 15 | x |  |  | x |  |  |
| Blood samples |  |  |  |  |  |  |  |
| Haematology, lipids, liver, kidney and endocrine function (TSH, glucose, hbA1c, inflammatory markers) | 10 | x |  |  | x |  |  |
| Questionnaires |  |  |  |  |  |  |  |
| HADS | 10 | x |  |  | x |  |  |
| SAQ | 10 | x |  |  | x |  |  |
| Ultrasound tests |  |  |  |  |  |  |  |
| Echocardiography (TTDE) | 40 |  | x |  |  | x |  |
| Coronary flow reserve (CFVR) | 60 |  | x |  |  | x |  |
| Stress echocardiography | 20 |  | x |  |  | x |  |
| Fat distribution and physical test |  |  |  |  |  |  |  |
| DEXA scan | 40 | x |  |  | x |  |  |
| VO_2_max test | 60 |  |  | x |  |  | x |
| Time consumption (hours) |  | ~5 | | 1 |  | | 1 |

## Primary endpoint

• Changes in coronary microvessel function assessed by a transthoracic Doppler echo (TTDE) measured CFVR

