## Figure 3. Project plan milestones

## Study participants

### Inclusion criteria

Patients will be recruited and included from the ongoing iPower study (please see figure 2)^28^ i.e.

- - Female gender
  - 40-75 years of age
  - Referred to a cardiac centre for assessment with coronary angiography due to chest pain or other signs of ischemia leaving out ST-segment elevation myocardial Infarction (STEMI) or NSTEMI patients (elevated enzymes, electrocardiographic (ECG) changes/no ECG changes)
  - No significant stenotic lesions at the following CAG defined as > 50% stenosis of epicardial vessels. Patients are included from the PATS database within 1 year after coronary angiography.
- Angina with a symptom burden of symptoms > monthly
- Impaired coronary microvascular function, defined as a TTDE measured CFVR < 2.5 with a good quality (quality index > 3)
- BMI > 25 (for BMI < 26 waist hip ratio must be > 0.8)
- Informed consent

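### The primary CFVR comparison is framed and sized as an unadjusted difference in change; naming baseline CFVR as a covariate would be a free improvement of uncertain size

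*Protocol*

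**What the plan says.** The Primary endpoint section of the Protocol gives "Changes in coronary microvessel function assessed by a transthoracic Doppler echo (TTDE) measured CFVR". The Sample size section repeats it: "The primary endpoint is change in microvascular function assessed by CFVR". The target there is a "difference in change in CFVR between groups of 10%, equal to a change in CFVR of 0.24", "assuming a baseline mean CFVR of 2.4", and "the standard deviation of the within individual change is assumed to be 0.3". It concludes: "With power of 0.8 and two-sided significance level of 0.05, 26 patients should be included in each group". It then adds: "Anticipating dropout, randomization of a total of 60 patients was chosen".

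Three other places bear on the point:
- The Blinding section places every baseline assessment before randomisation, and Table 1 lists CFVR at week 0 and week 24.
- The Inclusion criteria require "Impaired coronary microvascular function, defined as a TTDE measured CFVR < 2.5".
- The Randomization section describes permuted blocks and names no stratification by baseline CFVR.

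The only regression in the statistics section relates change in SAQ to change in CFVR. That is an association across women, not the randomised comparison. No between-group model for CFVR is given, with or without a covariate.

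**The concern.** A comparison of mean change subtracts the whole baseline value, so it treats the slope of follow-up on baseline as exactly 1. CFVR is measured with error, so that slope is likely to be below 1. A change score then over-corrects: if one arm starts higher by chance, part of that difference passes into the estimated effect with the opposite sign. With 26 to 30 women per arm and no stratification on CFVR, some imbalance is to be expected.

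At stake is precision in a small trial whose power is only just above 80% at 26 per group. The covariate that would help is already collected for every woman before allocation.

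**Working it through.** **Inputs from the Sample size section.** Difference 0.24 (10% of 2.4), SD of change 0.3, two-sided alpha 0.05, power 0.80, 26 per group. The documents give neither the baseline SD nor the slope or correlation between baseline and week 24. Both are assumed below.

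**1. The plan's own figure.** By the normal approximation, n = 2 × (1.96 + 0.84)² × 0.3² / 0.24² = 24.5, rounded up to 25. The t-test version gives 25.5, rounded up to 26, which matches. Power of the unadjusted t-test is 80.7% at 26 per group and 86.1% at 30.

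**2. Effect of adjustment.** Let s0 be the baseline SD and b the slope of follow-up on baseline. Then

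residual variance = 0.3² − s0² × (1 − b)².

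This is never larger than 0.09 and equals it only when b = 1. The cost is one degree of freedom (49 instead of 50 at 26 per group). At b = 1 power stays at 80.7%.

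**3. A narrow baseline.** The mean is assumed to be 2.4 and entry is capped at 2.5, so the average distance below the cap is 0.1. A tail of exponential shape would then have an SD of about 0.10 (assumed). Noncentral-t power at 26 per group:

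| Baseline SD (assumed) | b = 0.3 | b = 0.5 | b = 0.7 | b = 0.84 |
|---|---|---|---|---|
| 0.10 | 82.8% | 81.8% | 81.1% | 80.8% |
| 0.15 | 85.5% | 83.2% | 81.6% | 81.0% |
| 0.20 | 89.2% | 85.1% | 82.3% | 81.2% |

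Worked example: s0 = 0.10 and b = 0.5 give 0.09 − 0.01 × 0.25 = 0.0875, so the residual SD is 0.296.

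**4. Equal SDs at both visits.** Here b equals the correlation r, and the residual SD is 0.3 × √((1 + r)/2). The baseline SD this implies is 0.3/√(2(1 − r)).

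| r (assumed) | Residual SD | Power at 26 per group | Implied baseline SD |
|---|---|---|---|
| 0.3 | 0.242 | 93.9% | 0.25 |
| 0.5 | 0.260 | 90.4% | 0.30 |
| 0.7 | 0.277 | 86.6% | 0.39 |
| 0.84 | 0.288 | 83.8% | 0.53 |

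The value 0.84 is the repeat-examination reliability in the CFVR procedure section, used only as a stand-in for r.

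**5. Carry-over of imbalance.** A chance baseline difference of two standard errors at 26 per group is 2 × s0 × √(2/26) = 0.555 × s0. It shifts the change-score estimate by (1 − b) times that amount:
- s0 = 0.10, b = 0.5: 0.028.
- s0 = 0.20, b = 0.7: 0.033.
- s0 = 0.30, b = 0.5: 0.083, about a third of the 0.24 target.

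**The case against.** The strongest reply is that the Protocol fixes no unadjusted analysis. It names an endpoint and a sample size, not a test. Regressing change on arm and baseline gives the same arm effect as regressing week-24 CFVR on arm and baseline, so nothing already written would have to be reversed. Covariates are commonly left to the statistical analysis plan, which is not shown. All of this stands, and it makes the point an improvement rather than the correction of an error.

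Four stronger readings are tempting, and the documents do not support them:
- *The change score discards baseline.* It does not. It uses baseline with a fixed coefficient.
- *The sample size is wrong.* The figure of 26 per group reproduces. Sizing on the SD of change and then adjusting is, if anything, conservative.
- *Adjustment would lift power to about 87-94%.* Those figures need equal SDs at both visits and r between 0.7 and 0.3, hence a baseline SD of 0.25 to 0.39. That fits poorly with a mean of 2.4 under a cap of 2.5. If the week-0 CFVR is a fresh measurement not bound by the cap, a wider baseline is possible, but the argument from a restricted range then weakens.
- *The estimate is biased.* Under randomisation the change-score estimate is unbiased on average. Imbalance affects precision and the error in the particular sample drawn.

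A reader might also add that the repeatability coefficient of 0.70 implies an SD of differences of 0.70/1.96 = 0.357, above the assumed 0.3. That questions the SD assumption. It is a separate issue and no evidence for or against a covariate.

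**Conclusion.** The point holds as a free improvement. The endpoint and sample size rest on an unadjusted difference in change, and the statistics section names no baseline-adjusted comparison although a valid pre-randomisation covariate is available. The direction is secure: none of the scenarios shows a material loss, and the price is one degree of freedom. The size is not. At 26 per group, difference 0.24 and SD of change 0.3, the gain runs from almost nothing with a baseline SD near 0.10 (81-83%) to several points or more under equal SDs (84% at r = 0.84, 94% at r = 0.3). The documents do not give the two quantities that decide between these.

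**What to change.** State in the statistics section that the primary comparison is a linear regression of week-24 CFVR (equivalently, its change) on randomised arm with baseline CFVR as covariate, or confirm that the statistical analysis plan already specifies this. Keep the planned number of women, and do not reduce it on the strength of a gain that cannot be quantified. The cost is one sentence and one degree of freedom, with no new data.
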